In practice, high-concentration liposomal bupivacaine for brachial plexus blocks may cause prolonged motor blockade and potential phrenic nerve involvement, which could hinder early rehabilitation [21]. Although STB has been shown to preserve phrenic nerve function while providing comparable analgesia to interscalene block [20], no study to date has systematically evaluated different concentrations of liposomal bupivacaine specifically for STB. The optimal concentration that balances effective, prolonged analgesia with preserved motor function remains unknown. To address this research gap, this study aims to identify the optimal concentration of liposomal bupivacaine for STB in arthroscopic shoulder surgery, seeking to achieve effective and long-lasting analgesia while preserving shoulder joint mobility.

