### Randomization and blinding

An independent research coordinator, who will not be involved in the subsequent study, conducted the online randomization using a 1:1:1 allocation ratio and a permuted block size of 3. Subjects will be allocated to either Group A (liposomal bupivacaine 66 mg), Group B (liposomal bupivacaine 44 mg) or Group C (liposomal bupivacaine 33 mg) based on a random sequence (Figure 1). The doses were selected based on the following rationale. Notably, these dose selections remain partly exploratory, as robust pharmacodynamic and dose-response data for liposomal bupivacaine specifically in the superior trunk block (STB) are currently lacking. Nonetheless, the FDA-approved dose for interscalene block (ISB) is 133 mg. ISB targets the C5-C7 nerve roots at the interscalene groove. In contrast, STB is performed more caudally and laterally at the convergence of the C5 and C6 nerve roots, where they form the superior trunk of the brachial plexus. At this location, STB maintains comparable analgesia while allowing for lower local anaesthetic doses. Accordingly, we selected 66 mg (50% of the ISB dose) as the high-concentration group for STB. Second, 33 mg (25% of the ISB dose) was chosen to explore the minimal effective concentration. Third, 44 mg, the midpoint between 33 mg and 66 mg, was selected to identify the optimal balance between analgesia and motor function preservation. This trial is therefore designed to define the optimal concentration for STB. Allocation concealment will be ensured through the use of identical opaque sealed envelopes. An independent anaesthesia nurse at each study centre will be responsible for preparing the study medications. Given that varying concentrations of liposomal bupivacaine exhibit distinct appearances, we will maintain blinding for the surgeons and operating room staff by transferring the medication into identical opaque syringes, labelled solely with the patient’s identification number. The STB procedures will be conducted by a qualified anaesthesiologist, who will not participate in anaesthesia management or the supervision of postoperative care. All additional perioperative clinical care will adhere to the standard practices of the institution. Pertinent data will be documented in the trial case report form (CRF).

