### Sample size estimation

Sample size calculation was performed using PASS 2021 software (NCSS, USA) based on a previous study [24,25] and our preliminary data, with the goal of ensuring adequate power for both co-primary endpoints.

For the 48-hour moderate-to-severe pain incidence (dichotomized NRS): Based on our preliminary dose-finding results, the incidence of moderate-to-severe pain at 48 h was assumed to be 15% for Group A (66 mg), 25% for Group B (44 mg) and 35% for Group C (33 mg). Without optimized long-acting regional analgesia, approximately 74.3% of patients experience moderate-to-severe pain following arthroscopic rotator cuff repair [24,25]. Assuming 1-β = 0.8, α = 0.05 and *R* = 1, 84 participants per group are required.

For the co-primary outcome of cumulative 0–48 h opioid consumption (MME, continuous): Based on our preliminary data and published literature, the mean cumulative MME within 0–48 h was assumed to be 20 mg (SD = 12) in Group A, 35 mg (SD = 12) in Group B and 50 mg (SD = 12) in Group C. Using one-way ANOVA for three-group comparison with α = 0.05 and power = 0.8, 72 participants per group are required.

The larger requirement (84 per group) was adopted to provide ≥80% power for each co-primary endpoint. To allow for a 10% dropout rate, we will enrol 94 patients per group, resulting in a total sample size of 282 participants.

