### Statistical analysis

Normally distributed continuous variables will be presented as mean ± standard deviation (SD), non-normally distributed variables as median (interquartile range, IQR) and categorical variables as number (percentage).

For outcomes assessed at multiple time points, a linear mixed model for repeated measurements (MMRM) will be employed, with fixed effects including group, time point and the group × time interaction, patient as a random intercept, and pairwise comparisons between groups adjusted using Tukey’s correction. Missing data in repeated-measures analyses will be handled under the assumption of missing at random (MAR) using maximum likelihood estimation. The MMRM model naturally accommodates missing data without pre-imputation. A sensitivity analysis using multiple imputation will be conducted to test the robustness of results.

For single time point analyses, normally distributed continuous variables will be compared using one-way ANOVA, followed by post‑hoc pairwise comparisons with Tukey’s correction; non-normally distributed variables using the Kruskal‑Wallis test; and categorical variables using the chi‑square test or Fisher’s exact test as appropriate. Multivariable linear regression will be used to adjust for potential confounding factors, including age, sex, body mass index (BMI), baseline NRS score and surgical duration. A two-sided *P* value < 0.05 will be considered statistically significant.

For the trial to be declared positive regarding the primary hypothesis, both co-primary endpoints must reach statistical significance. Specifically, for at least one pairwise comparison, a statistically significant difference must be observed in both the 48-hour resting pain NRS score and the cumulative 0–48 h MME consumption, after applying Tukey’s correction for multiple comparisons within each endpoint. No additional alpha adjustment (e.g. Bonferroni) will be applied across the two co-primary endpoints. According to ICH E9 guidelines for co-primary endpoints, when a trial requires statistical significance on all co-primary endpoints to declare a positive result, the family-wise error rate is inherently controlled without further adjustment. This principle applies here, as both endpoints must demonstrate improvement to define a clinically successful analgesic regimen.

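### The success rule counts a difference in either direction although its own rationale requires improvement on both endpoints, and, being analgesic only, it does not identify an optimal concentration

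*Protocol article*

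**What the plan says.** The operative rule in the Protocol article, Statistical analysis, is that "for at least one pairwise comparison, a statistically significant difference must be observed in both the 48-hour resting pain NRS score". The sentence then sets the same condition for opioid use over the first 48 hours, with Tukey applied separately to each endpoint. The general criterion is two-sided: "A two-sided *P* value < 0.05 will be considered statistically significant". The rule names no reference group and no direction.

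The same paragraph closes its argument against any further alpha adjustment by stating that "both endpoints must demonstrate improvement to define a clinically successful analgesic regimen".

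The aim is wider than analgesia. The Introduction says: "The optimal concentration that balances effective, prolonged analgesia with preserved motor function remains unknown". Randomization and blinding says: "This trial is therefore designed to define the optimal concentration for STB", and explains the middle dose as the one meant to locate that balance. The Discussion describes the central question as one of sensory-motor dissociation rather than efficacy alone. Yet the motor and functional measures (MBS, Bromage, ASES) are secondary outcomes and have no part in the success rule.

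**The concern.** Two parts of one paragraph disagree. The rule asks for a difference; the rationale asks for improvement. A pair in which one group reports less pain but uses more opioid meets the first and fails the second. The trial could then be called positive on conflicting evidence, and the sentence that justifies the alpha handling would describe a condition that the rule does not impose.

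The rule is also narrower than the trial's question. A positive result means that one concentration gave better analgesia than another. It does not say where analgesia and motor function balance, so a report that moves from a positive trial to an optimal concentration would claim more than the rule tests. In a three-dose trial there is a further temptation to treat adjacent doses that do not differ significantly as interchangeable.

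**Working it through.** **Inputs from the protocol.** Sample size estimation: 84 evaluable per group; 48 h moderate-to-severe pain 15%, 25% and 35% in Groups A, B and C; mean MME 20, 35 and 50 mg with SD 12; "Assuming 1-β = 0.8, α = 0.05". Statistical analysis: Tukey within each endpoint, two-sided 0.05, same pair on both endpoints.

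**Assumptions made here.** Both endpoints are treated as normal with a common SD. NRS shifts are those that a normal latent score needs to give 15/25/35%. The correlation between endpoints is varied, since the protocol gives none.

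**1. The plan's own figure.** For 15% vs 35%, two-sided 0.05, 80% power:
- n₀ = [1.96·√(2·0.25·0.75) + 0.842·√(0.15·0.85 + 0.35·0.65)]² / 0.20² = 72.4
- with continuity correction: n = (72.4/4)·[1 + √(1 + 4/(72.4·0.20))]² = 82.1, so 83 per group

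This is within one of the stated 84. A three-group chi-square test would need 91. The pain sample size therefore matches a comparison of the highest with the lowest dose. Dropout: 84/0.9 = 93.3, so 94 per group and 282 in total, as stated.

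**2. What the rule accepts.** Suppose a pair X vs Y is Tukey-significant on both endpoints.

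| NRS lower in | MME lower in | Rule as written | Improvement on both |
|---|---|---|---|
| X | X | positive | yes, X |
| Y | Y | positive | yes, Y |
| X | Y | positive | no |
| Y | X | positive | no |

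**3. Pairwise effects.** The Tukey critical value is q(0.95; 3, 249)/√2 = 2.358. The standard error of a mean difference in SD units is √(2/84) = 0.154.
- NRS, latent: A–B = Φ⁻¹(0.25) − Φ⁻¹(0.15) = 0.362 SD; A–C = Φ⁻¹(0.35) − Φ⁻¹(0.15) = 0.651 SD; B–C = 0.289 SD
- MME, adjacent doses: 15/12 = 1.25 SD

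**4. Probability of a positive trial.** Simulation, at least 200,000 trials per scenario, 84 per group:

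| True state | Rule as written | Same group better on both |
|---|---|---|
| Both endpoints as planned (correlation 0, 0.3, 0.6) | 97% | 97% |
| MME as planned, NRS no effect | 4.8–5.0% | 2.5–2.6% |
| MME as planned, NRS reversed by 0.5 SD A to C (assumed) | 83% | <0.01% |
| Opposite trends of 0.3 / 0.4 / 0.5 SD A to C on the two endpoints (assumed), correlation −0.2 | 15 / 40 / 68% | <0.1% |
| The same, correlation +0.3 | 8 / 31 / 64% | <0.1% |

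The second row follows directly. With MME significant in practically every pair, success equals the chance that some NRS pair is Tukey-significant, which is 5% by construction, and about half of those results point the wrong way.

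**5. Which pair carries the result.** Under the planned effects, A vs C is significant on both endpoints in about 97% of trials, A vs B in about 50% and B vs C in about 32%. In about 25% only A vs C separates.

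**6. Adjacent-dose power at the Tukey threshold,** Φ(effect/SE − 2.358):

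| Measure | A vs B | B vs C |
|---|---|---|
| Dichotomized pain | 0.10/0.0612 = 1.633, power 23% | 0.10/0.0703 = 1.423, power 17% |
| Latent-normal NRS score | 0.362/0.154 = 2.346, power about 50% | 0.289/0.154 = 1.874, power about 31% |
| MME | 1.25/0.154 = 8.10, power >99.9% | the same |

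**The case against.** The strongest reply is that direction is not absent. The paragraph itself speaks of improvement, and a sensible analyst would read the rule in that light. Any concordant significant pair does show one dose better on both endpoints. This stands, and it makes the defect a contradiction between rule and rationale rather than silence. It does not cure it, because the operative sentence is the one that will be applied.

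A reader might infer from step 4 that 40% or more of positive declarations would rest on conflicting endpoints. The documents do not support that. The plan assumes that both endpoints move the same way with dose, and under its effects a discordant success has practically zero probability. Patients who take more opioid may report less pain, but such a trade-off within patients does not imply that randomized group means move in opposite directions. The only rescue drug that Anaesthesia management names is a non-opioid.

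A reader might also infer that the error rate is uncontrolled. It is not: requiring both endpoints keeps false success at about 5% at most in the scenario with one null endpoint.

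It can further be said that the rule governs an analgesic primary hypothesis, that motor outcomes are measured four times, that the protocol calls its dose choices partly exploratory, and that a selection rule with margins may sit in an analysis plan that is not shown. This too stands. The absence of such a rule is not the finding. What remains is that the article states the trial is designed to define the optimum while fixing success on analgesia alone.

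Finally, nothing in the protocol says that a non-significant 66 vs 44 mg comparison would be taken as equality, and that comparison is not unpowered throughout: MME has ample power on the plan's own inputs. The caution concerns pain only.

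**Conclusion.** The point holds as a should-fix. The rule contradicts the improvement statement in its own paragraph. Under the planned effects this makes no practical difference (97% either way). With MME as planned and no NRS effect, about half of the roughly 5% false successes would be discordant. The larger figures in step 4 depend on an assumed truth with opposite effects, which the plan does not expect.

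A positive result would come mostly through 66 vs 33 mg and would establish an analgesic difference, not an optimum. On pain, non-significance between adjacent doses would be weak evidence of similarity. The 31–50% power figures and the 97% rest on the latent-normal translation of the incidences; the 17–23% figures use the protocol's incidences directly, but for a dichotomized measure rather than the NRS score that the rule tests.

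**What to change.** 1. Restate the rule: for at least one pair, the same group must have both the lower 48 h rest NRS and the lower 0–48 h MME, each difference significant after Tukey at two-sided 0.05. This is one clause and has no power cost under the planned effects.

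2. State that a positive result shows an analgesic difference between concentrations. Label any statement about an optimal concentration exploratory, unless it follows a criterion that is fixed before unblinding and uses the motor outcomes already scheduled. If the full analysis plan holds such a criterion, a reference to it is enough. The cost is a more modest headline claim; no extra data are needed.

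3. Say that non-significance between adjacent doses will not be read as equivalence, and report those differences with 95% confidence intervals.

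Recruitment is planned from June 2026, so all three changes can be made as wording amendments before any unblinding.

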## Discussion

This study investigates the optimization of regional analgesia within ERAS protocols for shoulder arthroscopy, focusing on the balance between prolonged pain control and functional recovery. The shift from the traditional ISB to the STB is primarily motivated by the imperative to reduce iatrogenic morbidity, specifically HDP. By selectively targeting the superior trunk, STB significantly mitigates the risk of phrenic nerve palsy [17–20], enhancing patient safety-a cornerstone of the ERAS philosophy. This safety profile makes STB particularly advantageous for patients with pre-existing pulmonary compromise.

The incorporation of liposomal bupivacaine addresses the well-documented limitation of short-lived analgesia from single-injection nerve blocks. Its sustained-release formulation has demonstrated superiority over conventional local anaesthetics in providing pain relief during the critical 24 to 48-hour postoperative window and in reducing opioid requirements [14–16]. However, its extended duration of action presents a unique challenge in the context of peripheral nerve blocks: the potential for disproportionately long-lasting motor blockade. In shoulder surgery, where early passive and active motion is crucial for recovery, prolonged motor weakness could paradoxically impede rehabilitation progress and patient satisfaction, counteracting ERAS goals.

Existing literature offers limited guidance on employing liposomal bupivacaine in the STB approach. While its efficacy in ISB is established [14–16], the pharmacokinetics and optimal dosing for the more focused STB technique require dedicated evaluation. The central question is not merely whether it works, but at what concentration it provides an optimal sensory-motor dissociation – sufficient analgesia without undue motor impairment. This study directly addresses this gap by systematically evaluating different concentrations to define this therapeutic window.

The clinical implications of defining an optimal concentration are substantial. A successful regimen would yield a multimodal analgesic strategy that synergizes safety (low HDP risk of STB), efficacy (prolonged analgesia from liposomal bupivacaine) and functionality (preserved motor function for early mobilization). This aligns perfectly with the holistic aims of ERAS, potentially improving recovery quality, reducing opioid-related side effects and increasing patient satisfaction after shoulder arthroscopy.

This study has limitations. It primarily assesses pharmacodynamic outcomes (analgesia and motor function); larger-scale studies are needed to confirm the safety profile and precisely quantify the incidence of rare complications with this specific combination. Furthermore, the ideal concentration may vary based on surgical complexity (e.g. subacromial decompression vs. rotator cuff repair), suggesting a need for procedure-specific refinements in future research. Long-term follow-up would also be valuable to assess the impact of this analgesic approach on the development of chronic postoperative pain and final functional outcomes.

## Data Availability

The full protocol, participant-level dataset, statistical plan and informed consent materials can be available *via* contacting the corresponding author after the formal publication of this trial.
